# Effects of pre-transplant azithromycin administration on kidney graft function: study protocol for a double-blind randomized clinical trial

**DOI:** 10.1186/s13063-018-2744-y

**Published:** 2018-06-28

**Keywords:** Azithromycin, Kidney transplantation, Immunomodulation, Graft rejection, Transplant recipients

## Abstract

**Background:**

Kidney transplantation is the best strategy for the management of end-stage renal disease; however, the outcomes need to improve further. Macrolides show antimicrobial and anti-inflammatory properties in chronic diseases and intraoperatively, and can accumulate in tissues for extended periods. Therefore, theoretically, when administered to a donor and because of accumulation in the donor kidney, macrolides can cause graft immunomodulation and improve kidney transplantation outcomes.

**Methods:**

This study is a single-center, randomized clinical trial. A total of 60 kidney donors will be randomly allocated to the azithromycin or placebo group and treated with a single dose (1 g) of azithromycin or placebo, respectively, 1 day before surgery. Recruitment commenced in September 2016 and is expected to be completed by March 2018. The primary outcome is kidney graft function. The secondary outcomes include rejection rate, urinary tract infections in graft recipients, pain and systemic inflammatory response syndrome in live donors, and complications in both donors and recipients. Outcomes will be evaluated at baseline and every day in the first week after transplantation, as well as at 1 and 3 months post transplantation. Adverse reactions will be documented. If the efficacy of azithromycin in reducing adverse outcomes is confirmed, it would serve as an easy to use, economic intervention able to lower post-transplantation risks.

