### Participants

All procedures will be performed at Razi Hospital University Medical Center. All kidney donors considered for randomization would be informed of the study protocol. The standard preoperative screening of donors will include an examination by a nephrologist, a transplant surgeon, and an anesthetist. Renal ultrasonography, magnetic resonance angiography, or digital subtraction angiography will be performed to evaluate the vascular anatomy of the kidneys. If both kidneys are suitable for transplantation, the right kidney would be preferred. All recipients would undergo follow-up examinations every day for a week after surgery, and at 1 and 3 months post transplantation.

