### Sample size

The sample size was determined based on the fact that 36 subjects per group would appear adequate to provide estimates precise enough to meet our aim (pilot study) [20].

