### Inclusion criteria

Live or cadaveric donor.Informed consent form signed by the live donor or consent provided by the guardian or next-of-kin for a deceased donor.

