### Outcome measures

#### Primary outcome

The primary outcome will be the kidney graft function (evaluated using the glomerular filtration rate).

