### Statistical analysis

We will use standard descriptive statistics to assess baseline clinical and laboratory data at enrollment. Subsequently, we will compare creatinine levels at the end of each study period by using mixed models for repeated measures. Fixed factors will include the degree of human leukocyte antigen mismatch, age, sex, etiology of and baseline comorbidity, medication (azithromycin or placebo), and baseline laboratory test parameters (inflammatory and non-inflammatory markers). Complications, UTIs, and other outcomes will be similarly evaluated. Nominal data will be compared using the Student’s T test and categorical data will be compared using the χ^2^ test. Patients who drop out during the study period will be analyzed until the last hospital visit at which data are collected. *P* < 0.05 will be considered as a significant level. All data will be analyzed using SPSS software Version 20.

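### Donors are randomised but graft outcomes are analysed in recipients, and the analysis has no donor-level term if both kidneys of a deceased donor reach trial recipients

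*Protocol article*

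**What the plan says.** The abstract of the protocol article makes the donor the randomised unit: "A total of 60 kidney donors will be randomly allocated to the azithromycin or placebo group". The Interventions section agrees, since it is donors who are dosed. The Inclusion criteria admit a "Live or cadaveric donor", and the Interventions section describes a gastric-tube route for deceased donors, so their enrolment is planned.

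Follow-up and the main outcomes belong to the recipient. The Participants section says: "All recipients would undergo follow-up examinations every day for a week after surgery, and at 1 and 3 months post transplantation". The primary outcome is graft function by glomerular filtration rate. Rejection and recipient urinary tract infection are secondary outcomes.

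The Statistical analysis section says: "we will compare creatinine levels at the end of each study period by using mixed models for repeated measures". It lists the fixed factors, adds t tests and chi-square tests, and names no donor effect and no clustered variance.

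On how many kidneys per donor enter the trial, the only sentence is in the Participants section: "If both kidneys are suitable for transplantation, the right kidney would be preferred". Neither the inclusion nor the exclusion criteria set a number of recipients per donor.

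**The concern.** A deceased donor may supply two recipients. If both are in the trial, they have the same allocation by construction and share whatever the donor brings to the graft. Their outcomes are then likely to be positively correlated, and because treatment does not vary within the pair, that correlation goes straight into the variance of the treatment comparison. For recipient outcomes this would be a small cluster-randomised design.

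A repeated-measures mixed model handles correlation over time within one recipient. Without a donor term it does not handle correlation between two recipients of one donor. The t and chi-square tests assume independent observations throughout. At stake are confidence intervals that are somewhat too narrow and a true type I error above the stated 5%, in a small trial where a borderline result could be tipped over the threshold.

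**Working it through.** The plan has no variance, correlation or design effect of its own to reproduce, and the Sample size section gives no effect size, standard deviation or power. The check therefore asks how large the error would be under stated assumptions.

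**Inputs**
- Donors randomised: 60 (abstract).
- Significance level: 0.05 (Statistical analysis); two-sided is assumed.
- s, the share of recipients who share a donor with another trial recipient: not in the document; assumed 0.25 to 0.5.
- ICC, the within-donor correlation of the recipient outcome: not in the document; assumed 0.2 to 0.4.

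**Formulas**
- With n_j recipients from donor j and N recipients in all, the variance of an arm mean is inflated by 1 + ICC × Σ n_j(n_j − 1)/N. A pair adds 2 to the sum and a single recipient adds 0, so the sum divided by N equals s. Hence DE = 1 + s × ICC.
- Shortfall of the naive standard error = 1 − 1/√DE.
- Actual type I error = 2[1 − Φ(1.96/√DE)].

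**Results**

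| s | ICC | DE | SE too small by | 1.96/√DE | Type I error |
|---|---|---|---|---|---|
| 0 | any | 1.00 | 0% | 1.960 | 5.0% |
| 0.25 | 0.2 | 1.05 | 2.4% | 1.913 | 5.6% |
| 0.25 | 0.4 | 1.10 | 4.7% | 1.869 | 6.2% |
| 0.5 | 0.2 | 1.10 | 4.7% | 1.869 | 6.2% |
| 0.5 | 0.4 | 1.20 | 8.7% | 1.789 | 7.4% |

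**What s means in donors.** If 20 of 60 donors gave two kidneys to trial recipients, there would be 60 + 20 = 80 recipients, 40 of them in pairs, so s = 0.5. With 9 such donors there would be 69 recipients, 18 of them in pairs, so s is about 0.26.

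**Check by simulation.** A t test under no treatment effect, with 30 donors per arm and 20,000 runs, agrees with the formula:
- One fifth of donors giving two kidneys, ICC 0.3: s = 0.4/1.2 = 0.333 and DE = 1.10. Simulated 5.9%, formula 6.2%.
- Half of donors giving two kidneys, ICC 0.3: s = 1/1.5 = 0.667 and DE = 1.20. Simulated 7.2%, formula 7.4%.

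**The case against.** The strongest reply is that nowhere does the article say that two recipients of one donor enter the trial. The right-kidney sentence points towards one kidney per donor, and the paragraph around it speaks of donors generally, not only live ones. The words about all recipients introduce a visit schedule and need not mean that both recipients of a donor are included. The article lists only fixed factors, so a fuller plan might contain a donor random effect.

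Much of this stands, and it is why the point must be conditional. It does not remove the point. The right-kidney sentence follows a work-up by nephrologist, surgeon and anesthetist with vascular imaging, which fits live donors best, and it states a preference, not a limit on trial recipients. The article does commit to specific tests, and t and chi-square tests cannot accommodate pairs whatever a fuller plan says about random effects.

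Three stronger readings are tempting, and the document does not support them:
- **That standard errors will certainly be too small.** This needs pairs to occur and to be positively correlated; the document states neither.
- **That every recipient is in a pair.** With ICC 0.4 this would give DE = 1.40, a naive standard error 15.5% too small and a type I error of 9.8%. It would require every donor to be deceased, yet live donors are eligible, are dosed orally and have their own secondary outcomes.
- **That 36 per group (72 in all) against 60 donors shows pairing.** The figures would fit 12 donors giving two kidneys, but the article does not say so. The mismatch exists with or without clustering and is a separate issue.

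The concern also does not touch donor pain, systemic inflammatory response or donor complications, which are analysed in the randomised unit.

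**Conclusion.** The point holds conditionally. The unit of randomisation is the donor, the main outcomes are the recipient's, the number of trial recipients per deceased donor is not limited, and the stated analysis makes no provision for two recipients sharing a donor. If pairs enter, the recipient analyses as written would be somewhat anti-conservative: a type I error of about 5.6% to 7.4% instead of 5%, over the assumed quarter to half of recipients in pairs and correlation of 0.2 to 0.4. The calculation is unadjusted; the fixed factors in the mixed model could lower the residual correlation and hence the error. If each donor contributes one recipient, the error is zero. The size is modest and rests on assumed inputs, but the gap is in the stated analysis and is cheap to close.

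**What to change.** In the Statistical analysis section:
- State how many trial recipients a randomised donor can contribute.
- Add a donor random intercept, with recipients nested in donor, to the repeated-measures mixed model.
- For binary recipient outcomes such as rejection and urinary tract infection, replace the plain chi-square test with donor-clustered GEE or donor-clustered robust standard errors. Treat any recipient outcome compared by t test in the same way.
- Report the numbers of donors and recipients separately by arm, with the number of donors contributing two recipients.
- State in advance that the donor term is dropped if no donor contributes two recipients, because it then cannot be separated from recipient-level variation.

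The cost is a donor identifier in the dataset, which the article does not mention, and slightly wider confidence intervals where pairs occur. Enrolment, treatment and visits are unchanged.

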**Discussion:**

Short and mid-term analyses of blood and urine samples as well as immunological assays will facilitate a more in-depth analysis of the effects of azithromycin on transplantation outcomes.

**Trial registration:**

Iranian Clinical Trial Registry, IRCT201606141853N11, registered on September 5, 2016.

**Electronic supplementary material:**

The online version of this article (10.1186/s13063-018-2744-y) contains supplementary material, which is available to authorized users.

## Background

The incidence and prevalence of end-stage renal disease necessitating dialysis or transplantation has not changed in the past few decades, with these even increasing in developing countries, wherein healthcare needs to be improved in line with the burden of disease [1, 2]. Compared to dialysis, a kidney transplant affords significantly better survival and quality of life to end-stage renal disease patients, making transplantation one of the most cost-effective surgeries [3]. Therefore, preventing graft loss after kidney transplantation is crucial.

The immunomodulatory properties of antibiotics such as macrolides have been studied and reported [4–6]. Azithromycin is a member of the macrolide (azalide) family and its blood serum concentration can be ≥ 100-fold that in body tissues, especially in leukocytes [7, 8]. It can accumulate in body tissues for up to a month even following administration of a single dose [9]. Therefore, azithromycin administered to kidney donors may persist in transplanted kidney cells, especially in the immune cells of the grafted kidney.

Mammalian target of rapamycin (mTOR) is a cytoplasmic protein that plays a key role in the activation of immune cells following foreign stimulation and is now believed to be a major immune system controller [10], making rapamycin one of the most important drugs in transplantation [11]. Ratzinger et al. [11] showed that azithromycin exerts an immunomodulatory effect on CD4 (+) T-cells by preventing mTOR activity. Thus, administration of azithromycin prior to a transplant can result in prolonged drug accumulation in the kidney and modulate inflammatory processes locally.

The immunomodulatory influence of macrolides has been shown to lower the expression of inflammatory genes [12] and affect the production and efficacy of many pro-inflammatory cytokines such as interleukin (IL)-1, IL-6, IL-8 and tumor necrosis factor [13, 14]. Chemoattractant and inflammatory molecules have been reported to be crucial determinants in kidney rejection [15, 16]. Azithromycin can limit the signaling of chemoattractants such as IL-8 and reduce the production of inflammatory molecules such as granulocyte macrophage colony-stimulating factor, which contribute to neutrophil attraction to inflamed organs. Thus, the anti-inflammatory action of macrolides can prevent leukocyte infiltration into the transplanted kidney.

To our knowledge, no published study has evaluated the effects of macrolide administration in kidney donors on outcomes in kidney recipients. Azithromycin administration to cadaveric or live donors can theoretically result in drug accumulation in the donated kidney, where it exerts an immunomodulatory effect and can reduce preoperative adverse outcomes such as rejection. The effects of azithromycin in other organ transplantations have been previously shown. Azithromycin therapy following keratoplasty yielded results similar to those achieved with topical dexamethasone, without the risk of adverse effects commonly associated with steroidal drugs and enhanced graft survival in rats [17]. A study found that azithromycin promoted the survival of high-risk corneal allografts, apparently without modulating the immune system [18]. Iwamoto et al. [19] reported that azithromycin, with its immunomodulatory properties, is a potential prophylactic drug for the lethal graft-versus-host disease.

In this study, we will assess the safety and efficacy of azithromycin administration to kidney donors and its effects on both donor and recipient outcomes.

## Methods

### Overview of the study design

We designed a double-blind randomized clinical trial (RCT). The interventions will be performed at an academic institution, The Affiliated Hospital of the Guilan University of Medical Science, Guilan, Iran.

### RCT flow chart

Prior to inclusion, all participants will be screened at the Urology Research Center and will then be randomized into the azithromycin or placebo group. Following randomization, the participants will receive 1 g of azithromycin or placebo 1 day before surgery. The outcome will be evaluated by investigators blinded to the group randomization, during the study. Adverse events will be documented for safety assessment.

The study protocol has been reviewed and approved by local institutional review boards and ethics committees. The trial adheres to the principles of the CONSORT (Fig. 1), the Standard Protocol Items: Recommendations for Interventional Trials (SPIRIT) (Fig. 2) (checklist as an Additional file 1), and the Declaration of Helsinki (sixth revision, 2008).

**Fig. 1 Fig1:**
[figure not shown]
Consolidated Standards of Reporting Trials (CONSORT) diagram showing the flow of participants through each stage of a randomized trial

**Fig. 2 Fig2:**
[figure not shown]
Standard Protocol Items: Recommendations for Interventional Trials (SPIRIT)

### Participants

All procedures will be performed at Razi Hospital University Medical Center. All kidney donors considered for randomization would be informed of the study protocol. The standard preoperative screening of donors will include an examination by a nephrologist, a transplant surgeon, and an anesthetist. Renal ultrasonography, magnetic resonance angiography, or digital subtraction angiography will be performed to evaluate the vascular anatomy of the kidneys. If both kidneys are suitable for transplantation, the right kidney would be preferred. All recipients would undergo follow-up examinations every day for a week after surgery, and at 1 and 3 months post transplantation.

### Sample size

The sample size was determined based on the fact that 36 subjects per group would appear adequate to provide estimates precise enough to meet our aim (pilot study) [20].

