### Randomization

Participants will be randomly assigned to either the azithromycin or placebo group by using the method of random permuted blocks [21].

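### The article gives two incompatible planned sizes, 60 donors in total and 36 subjects per group (72), and justifies only the second.

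*Protocol article*

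**What the plan says.** The Abstract (Methods) fixes the size as a total, counted in donors: "A total of 60 kidney donors will be randomly allocated to the azithromycin or placebo group". The Sample size section fixes it per group, counted in subjects, and gives its whole justification in one clause: "36 subjects per group would appear adequate to provide estimates precise enough to meet our aim (pilot study", with a literature reference. It states no SD, effect size, power or target interval width.

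The Randomization section confirms two groups: "Participants will be randomly assigned to either the azithromycin or placebo group by using the method of random permuted blocks". It gives no allocation ratio. The primary outcome is continuous, namely graft function measured by GFR. The Statistical analysis section says how dropouts are handled ("Patients who drop out during the study period will be analyzed until the last hospital visit at which data are collected") but gives no dropout rate and no inflation of the sample size.

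On aim, Sample size calls the trial a pilot sized for estimation. The Abstract describes what would follow "If the efficacy of azithromycin in reducing adverse outcomes is confirmed".

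**The concern.** Two groups of 36 make 72, not 60, so both figures cannot be the planned size. The planned number determines what recruitment aims for and what a reader later holds the trial to. As the article stands, a final count of 60 could be read as meeting the target or as falling 12 short of it.

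The conflict also affects the justification. The argument about precision is attached to 36 per group. If 60 is the real plan, the article gives no argument for it.

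A smaller matter follows from the same section. A trial described as a pilot sized for estimation sits awkwardly with an Abstract that looks ahead to confirmed efficacy.

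**Working it through.** **Inputs from the article.** Total of 60 donors (Abstract, Methods). 36 subjects per group (Sample size). Two groups (Randomization). Significance level 0.05 (Statistical analysis).

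**Assumptions.** 1:1 allocation, a two-sided test, and an unadjusted comparison of two means. The article states neither the ratio nor the sidedness.

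**Step 1: can 36 per group be reproduced?** No. Without an SD, effect, power or interval width there is nothing to derive it from.

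**Step 2: do the two sizes agree?** 2 × 36 = 72. 72 − 60 = 12, and 12/72 = 16.7%. Per group, 60/2 = 30, which is 6 fewer than 36.

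**Step 3: can anything reconcile them?**

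- *Dropout.* 30/(1 − d) rounds up to 36 for d between 15% and 16.7%; for example, 36 × (1 − 1/6) = 30. But no rate is stated, and under this reading 72 would be randomised with about 60 evaluable. The Abstract says 60 are randomised.
- *Unequal allocation.* Two groups of 36 total 72 by definition, so no ratio yields 60.
- *Donors versus recipients.* If the subjects were recipients, 72 − 60 = 12 donors would each have to supply two kidneys, and the split would have to give exactly 36 recipients per group. Deceased donors are eligible, so this is conceivable. However, donors are the randomised unit (Participants: "All kidney donors considered for randomization would be informed of the study protocol"), and nothing says that the 36 are recipients or that 12 double donations are planned.

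**Step 4: what does the difference cost in precision?** The 95% CI half-width for a difference in two means, in SD units, is t(0.975; 2n − 2) × √(2/n).

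| n per group | t | √(2/n) | Half-width (SD) |
|---|---|---|---|
| 30 | 2.0017 | 0.2582 | 0.517 |
| 36 | 1.9944 | 0.2357 | 0.470 |

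The ratio is 0.5168/0.4701 = 1.099, about 10% wider with 30 per group. The normal approximation gives 0.506 against 0.462, and √(36/30) = 1.095.

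The article gives no SD for GFR, so absolute widths are only illustrative:

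| Assumed SD (GFR units) | Half-width, 30 per group | Half-width, 36 per group |
|---|---|---|
| 10 | 5.2 | 4.7 |
| 15 | 7.8 | 7.1 |
| 20 | 10.3 | 9.4 |

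The relative widening of about 10% does not depend on the SD.

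**The case against.** The strongest reply accepts the mismatch but limits what may be built on it. Four points deserve an answer.

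1. *A reader might infer that 60 misses the precision the plan needs.* The article does not support that. It states no required precision and says only that 36 per group seems enough, which is sufficiency and not a minimum. Nor does it show that 72 is the right figure and 60 the slip; the error could lie in either section. This point stands.

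2. *A reader might infer that neither size could confirm an effect on rejection, urinary tract infection or complications.* That is not shown either. Power depends on event rates that the article does not give. By normal approximation with assumed rates, power at 30 and 36 per group is 25% and 29% for 15% against 5%, but 78% and 85% for 40% against 10%. Low power for modest effects is likely, but a flat statement of impossibility goes too far. These are also secondary outcomes.

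3. *A reader might infer that recruitment has no defined end.* The Abstract and Trial status both give March 2018. What is unclear is the target number, not the calendar.

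4. *The half-widths are not those of the planned analysis.* The Statistical analysis section specifies mixed models for repeated measures with covariates, so the widths in SD units describe a simpler comparison. This is correct, and the figures should be read as a comparison between the two sizes.

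A further reply is that a journal article condenses the full protocol. That would excuse a missing calculation. It does not excuse two printed figures that contradict each other. Finally, the Abstract's sentence about efficacy is conditional, so its tension with the pilot aim is a matter of wording, secondary to the contradiction in size.

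**Conclusion.** The contradiction holds and needs correcting: 60 donors in total and 36 subjects per group cannot both be the planned size, and no statement in the article reconciles them. The difference is 12 subjects. Because the only justification belongs to the larger figure, a trial of 60 has no stated basis.

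The measurable consequence is modest: 95% intervals about 10% wider at 30 per group, assuming 1:1 allocation and an unadjusted comparison. The finding goes no further. Whether 30 per group is too few cannot be judged from a document that sets no precision target.

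**What to change.** State one planned number in both the Abstract and Sample size, with its unit: donors randomised in total and per group, and the number of recipients expected from them. Take it from the approved plan, not from the count eventually reached.

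If 60 stands, rewrite Sample size as 30 per group and report the precision it delivers. In SD units this needs no outside figure: a half-width of about 0.52 SD for an unadjusted 1:1 comparison. If 72 stands, correct the Abstract and report about 0.47 SD. If the gap reflects expected losses or donors giving two kidneys, say so and give the assumed rate or number.

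Replace the Abstract's reference to confirmed efficacy with wording that fits a pilot, such as estimates with 95% confidence intervals to inform a confirmatory trial.

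The cost is a few sentences. No procedure or analysis changes. If 60 is kept, the precision reported is about 10% less favourable than at 36 per group.
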